**Methods:**

The study will involve 140 teeth with apical periodontitis and fistulas. The teeth will be randomly assigned to one of two treatment groups. Group I will receive only the conventional endodontic treatment, which includes root canal cleaning, shaping, and obturation. Group II will undergo the same conventional endodontic treatment, but with an additional step of aPDT. The aPDT procedure involves applying a photosensitizer to the root canal and irradiating it with light to produce reactive oxygen species. Each group will consist of 70 teeth to ensure adequate statistical power. The primary outcome is fistula resolution, assessed clinically at 15 and 30 days post-treatment. The secondary outcome is the comparison of apical radiolucency from periapical radiographs to evaluate healing and reduction of periapical pathology.

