### Interventions

All participants will be treated by the same experienced endodontist, who will oversee both data collection and procedural management. Each participant will receive conventional treatment.

A baseline periapical radiograph will be required for all participants, as well as follow-up radiographs at 15- and 30-days post-treatment. These radiographs will be obtained by a different operator, who will analyze them. This operator will be blinded to the intervention received by each participant.

Conventional treatment will be performed using the Protaper rotary system (Dentsply Maillefer rotary instruments). The canal irrigation will be with 5% sodium hypochlorite, 17% ethylenediaminetetracetic acid, and 2% chlorhexidine [14]. Subsequently, a methylene blue solution in a surfactant medium will be applied using a size 30 paper point cone (Dentsply), with a pre-irradiation time of 1 minute. The study group will receive a 3-minute irradiation period, while the control group will be administered the photosensitizer along with a simulated laser application. This simulation will be achieved by placing an aluminum foil barrier at the tip of the laser equipment to block the light. During these procedures, both the operator and participants will wear protective eyewear to ensure eye safety and concealment. Calcium hydroxide will be applied to the root canals as a long-term intracanal dressing for endodontic treatment.

A diode laser device (Therapy EC, DMC, São Carlos, Brazil) with a wavelength of 660 nm and a power output of 100 mW will be used, according to the parameters detailed in Table 1. The pre-irradiation and irradiation durations will be identical for both groups.

**Table 1 pone.0315169.t001:** Dosimetric parameters.

PARAMETERS	
Wavelength (nm)	660
Operating mode	Continuos
Power (mW)	100
Irradiance (mW/cm^2^)	250
Target irradiated area (cm^2^)	0.4
Exposure time (s)	180
Radiant exposure (J/cm^2^)	10
Energy (J) per point	18
Number of irradiated points	2
Application technique	Entry duct and fistula
Number of sessions	1

The photosensitizer used will be methylene blue at a concentration of 0.005%, dissolved in 0.25% sodium dodecyl sulfate.

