### Sample size calculation

The sample size calculation was conducted with the statistical software G-Power 3.1 (Universität Kiel, Germany) applying the chi-square homogeneity test. Identical sample sizes were determined for both the aPDT group and the sham group. A type I error rate of 5% and a statistical power of 80% were specified [15], resulting in a required sample size of n = 70, accounting for a 10% loss to follow-up. The sample size calculation was based on established literature, and a significance level of 5% will be employed [8, 13, 16].

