### Statistical analysis

The distribution of data within each group will be checked. The categorical variables will be analyzed using the Pearson Chi-square test or two sample t-test. The correlation between clinical or radiographic findings and the healing fistula will be analyzed by Pearson Chi-square test or Mann Whitney U test [13].

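### The stated test for fistula resolution is a valid unadjusted chi-square that leaves out baseline radiolucency, which the trial must read anyway; adjusting for it would cost little, with an uncertain gain of about 0 to 7 power points

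*Protocol article*

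**What the plan says.** The Statistical analysis section of the Protocol article gives one rule for categorical outcomes: "The categorical variables will be analyzed using the Pearson Chi-square test or two sample t-test". Fistula resolution is yes or no, so the applicable part is the chi-square. The Sample size calculation section agrees, having been done by "applying the chi-square homogeneity test". The Randomization section describes a web randomiser and sealed envelopes and names no stratification factor. No covariate appears anywhere in the article.

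Baseline radiographic information is nevertheless required:

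- Study design makes apical radiolucency on the initial film an entry condition.
- Interventions states: "A baseline periapical radiograph will be required for all participants". It assigns the radiographs to a separate operator who is blinded to treatment.
- Primary outcomes lists radiographic improvement, judged by change in periapical radiolucency, with no restriction to teeth whose fistula has healed.

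The Statistical analysis section also plans a separate look at association: "The correlation between clinical or radiographic findings and the healing fistula will be analyzed by" a chi-square or Mann-Whitney test.

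**The concern.** A baseline reading taken before treatment and available for every tooth is a natural covariate. If it is related to closure, leaving it out of the treatment comparison costs power and leaves any chance difference between the arms in lesion status uncorrected. With no stratification stated, such differences will sometimes arise. If one is noticed only after the data are in, adjusting for it then is post hoc and open to challenge. The stake is efficiency and robustness of the primary comparison, not its validity.

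**Working it through.** **Inputs from the document.** "A type I error rate of 5% and a statistical power of 80% were specified"; "resulting in a required sample size of n = 70, accounting for a 10% loss to follow-up"; and, from the abstract, "Each group will consist of 70 teeth to ensure adequate statistical power". Evaluable teeth per arm: 70 × 0.9 = 63, or 126 in total.

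**The plan's own figure.** It cannot be reproduced, because no closure rates or effect size are given; the section says only "The sample size calculation was based on established literature, and a significance level of 5% will be employed". Working backwards with a non-central chi-square on 1 degree of freedom, w = 0.25 gives a non-centrality of 126 × 0.25² = 7.875, hence 80% power, and 126 / 0.9 = 140. That matches 70 per arm, but w = 0.25 is inferred, not stated.

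**Assumed closure rates.** 60% v 83% is close to that effect: w = (0.23 / 2) / √(0.715 × 0.285) = 0.115 / 0.451 = 0.255. Exact enumeration at 63 per arm gives 83.1% power for the crude chi-square. The prognostic strength of baseline radiolucency is also an assumption, so a range is shown.

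**Power, crude v adjusted.** Simulations had 3,000 runs per scenario, 63 teeth per arm and one standard normal baseline covariate. The adjusted test is the likelihood-ratio test for arm in a logistic model with that covariate. The last column repeats the exercise at 50% v 73.8%, 60% v 82.4% and 70% v 89.7%, each with crude power of about 80%.

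| Odds ratio per SD | Crude, 60% v 83% | Adjusted | Gain (points) | Gain at the three other rate pairs |
|---|---|---|---|---|
| 1 | 83.9% | 84.3% | 0.4 | -0.3 to 1.0 |
| 1.5 | 81.0% | 82.2% | 1.2 | 0.9 to 2.4 |
| 2 | 83.9% | 86.8% | 2.9 | 2.3 to 3.9 |
| 3 | 82.4% | 89.4% | 7.0 | 6.4 to 7.1 |

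A separate simulation at 60% v 83% gave gains of about 0, 1, 3 and 6 points. Under no treatment effect, rejection rates were about 5% to 6% for both the crude and the logistic test.

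**Precision.** Crude power should be 83.1% in every row at 60% v 83%, yet it ranges from 81.0% to 83.9%. Both tests were run on the same simulated data sets, so each gain is more reliable than either power figure. Even so, the small gains should be read as rough.

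**What the gain is worth.** Required n is proportional to (1.96 + z)², where z is the normal quantile of the power.

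- From 80% to 83%: (1.96 + 0.954)² / (1.96 + 0.842)² = 1.08, or about 10 more teeth on 126.
- From 80% to 87%: (1.96 + 1.126)² / (1.96 + 0.842)² = 1.21, or about 27 more.

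**Chance imbalance.** The difference between arms in covariate mean has SD √(2/63) = 0.178 in SD units. The probability that it exceeds 0.25 SD in either direction is 2 × (1 − Φ(0.25 / 0.178)) ≈ 16%.

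**Can the model be fitted?** At 60% v 83%, the expected number of open fistulas is 63 × 0.40 + 63 × 0.17 = 25.2 + 10.7 ≈ 36. At 70% v 89.7% it is 63 × 0.30 + 63 × 0.103 = 18.9 + 6.5 ≈ 25. Either is adequate for arm plus one covariate.

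**The case against.** The strongest objection is that nothing here is an error. A Pearson chi-square on a binary outcome is valid under 1:1 randomisation, its 5% error rate already allows for chance imbalance, and it matches the test used to size the trial. All of that stands. A reader might infer that chance imbalance makes the planned comparison biased or unsound; the document gives no ground for that.

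A reader might also infer that lesion size is already recorded for every tooth. It is not stated. A film is required and radiolucency must be read, but no size measure, scale or unit is defined. The restriction to healed fistulas under Secondary outcomes does not remove the baseline reading, because the entry condition and the second primary outcome apply to all teeth.

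Nor does the planned correlation analysis show that the trial team expects radiolucency to predict closure. Testing an association is not expecting one, and the findings tested could be those at 15 or 30 days, which could not serve as covariates. Prognostic strength is therefore assumed throughout, and at an odds ratio of 1.5 per SD the gain is only about 1 to 2 points.

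Finally, an adjusted model may sit in an analysis plan that is not shown. That is possible. The article does, however, state a method for this outcome, and the point is a better choice in place of that method, not a complaint about missing detail.

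**Conclusion.** The concern holds as an inexpensive improvement to a valid analysis. The only stated between-arm test for fistula resolution ignores a baseline reading that the trial must make anyway. Prespecified adjustment would add about 0 to 1 power points if radiolucency is unrelated or weakly related to closure, about 3 at an odds ratio of 2 per SD, and about 6 to 7 at an odds ratio of 3, with type I error near 5%. It would also deal in advance with a chance imbalance. These figures rest on 63 evaluable teeth per arm, assumed closure of 60% v 83%, and an assumed prognostic strength; the document supports neither of the last two. The case for acting is the asymmetry: almost nothing is lost if the covariate proves uninformative.

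**What to change.** Amend the Statistical analysis section before recruitment opens, which the article places after acceptance of the protocol for publication:

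- Define one baseline radiolucency measure, for example the largest lesion diameter on the baseline film, read by the blinded operator already planned.
- Make the analysis of fistula resolution a logistic regression on randomised arm with that measure as covariate, tested at the two-sided 5% level and reported as a standardised risk difference with 95% CI.
- Keep the crude Pearson chi-square as a supporting analysis.
- If a fallback is wanted for sparse data, such as a Mantel-Haenszel test stratified by baseline size, trigger it by a number of open fistulas fixed in advance and counted over both arms pooled. An unquantified trigger would let the test be chosen after outcomes are seen.

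The sample size stays at 70 per arm, and no extra participants, visits or films are needed. The cost is that the measure and its reading rules must be written down beforehand, with little or no return if it proves not to be prognostic.

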## Discussion

aPDT is considered a complementary approach in endodontic treatment. A primary limitation of this technique is the formation of compounds that can reduce the efficacy of the therapy. This group has been studying these compounds for several years [12, 17, 18].

On the other hand, SDS demonstrated the ability to mitigate the effect of dimer formation [19]. Therefore, this study aims to evaluate the effectiveness of methylene blue combined with 0.25% SDS in photodynamic therapy for treating apical periodontitis with fistulas. The objective is to assess how effectively this combination eliminates persistent microorganisms in root canals [8].

This study addresses the challenge of treating teeth with fistulas, which often require several clinical sessions. The main difficulty is effectively eliminating the bacteria that reside within the root canals of these teeth [4].

aPDT is a non-invasive therapeutic modality that can be employed as an adjunctive treatment for apical periodontal diseases. It reduces the reliance on systemic antimicrobials, thereby mitigating the risk of antimicrobial resistance associated with these medications.

Unlike antibiotics, aPDT exhibits low toxicity to humans and is not associated with the development of bacterial resistance [20]. Given the issue of antibiotics and their indiscriminate use by patients, it is essential to seek alternative and adjunctive methods for combating microorganisms. This is particularly pertinent in countries where, despite legislation regulating antibiotic sales, patients can still obtain these medications easily without prior consultation or authorization from a healthcare professional.
